### Study participants

The study’s total targeted enrollment is 400 18-65-year-old men and women who meet DSM-IV defined criteria for current major depressive disorder (MDD) and who have never previously received treatment for a mood disorder. Patients with acute, recurrent, or chronic MDD are included. The study excludes psychotic subtype of MDD, seasonal affective disorder, and pregnant or breast-feeding women. All interested patients undergo a telephone screening to assess preliminary eligibility, and potentially eligible patients are then scheduled for an in-office screening visit. Patients are not paid for participation during the acute phases, but they do receive the equivalent of approximately $5 per visit to offset travel-related costs. Patients entering into the follow-up phase receive $50 per visit to compensate for their time and inconvenience. The fundamental reason for examining treatment-naïve patients is to avoid confounding the biology of the illness with the effects of previous treatment, an effect that might result in persistent biological changes. Although the strictest definition of treatment-naïve would be patients who have not received a single dose of an antidepressant/psychotropic or a single session of formal individual psychotherapy, defining treatment naiveté so strictly is unnecessarily restrictive and reduces the feasibility of recruiting the targeted number of subjects. We have therefore operationalized previous treatment (and therefore study ineligibility) as treatment for MDD, dysthymia, or depressive disorder not otherwise specified with either: (1) a marketed antidepressant at a minimum effective dose for 4 or more consecutive weeks; or (2) four or more sessions of an established structured psychotherapy for depression, that is CBT, behavior therapy, interpersonal therapy (IPT), or behavioral marital therapy. Patients who have received supportive therapy or other forms of therapy are eligible, regardless of the duration of their previous psychotherapy course.

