Patients who do not remit (that is, those with an HDRS-17 total score of ≥8 at either week 10 or week 12) following 12 weeks of monotherapy are offered the option to enter an additional 12-week course of combination treatment. Patients who initially received a medication as monotherapy continue on that medication in a double-blind manner, and begin the 16-session course of CBT. Patients who initially received CBT will have open-label escitalopram added to their treatment, following the same dosing guidance as described for the monotherapy treatment. We chose to use open-label medication in this phase due to inadequate power to identify differences between randomized treatments. These patients also meet with their CBT therapist once per month for a total of three monthly booster sessions over this 12-week period. The visit structure for this combination phase treatment replicates that of the monotherapy phase: weekly ratings visits for 6 weeks, followed by bi-weekly ratings visits for the next 6 weeks. At the end of this 12-week combination treatment period (that is, week 24 from baseline), patients are assessed for response to the combination treatment (see below). Those who remit or respond (defined below) can continue into the long-term follow-up phase (described below) for an additional 18 months, following the same visit schedule as the monotherapy phase remitters.

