#### Statistical power/sample size

There are no established ways to determine sample size for the identification of possible predictors of an outcome, as it is a fact-finding endeavor and does not test specific *a priori* hypotheses. However, the issue of clinical importance is much more paramount in a study of this nature (that is, while statistically significant predictors are of interest, it is also necessary to determine if the predictors of interest result in a large enough absolute or relative difference in response between those with and without the predictor to be clinically meaningful)
[135]. In addition, it is clear that smaller but statistically significant effects will likely be difficult to replicate and thus reduce the validity of the model for future use. Given the sample size we intend to recruit over the time period specified, we will illustrate the effect sizes for treatment remission versus non-remission, as very few data on differential treatment response are available. For these calculations, we assume a 40% remission rate. The detectable difference is defined as the difference (either mean or proportion) between the population and the treatment remitters detectable with the given sample size, a Type I error rate (α) = 0.01, and a statistical power of 0.80. We chose an α = 0.01 because the nature of the model building will require the testing of multiple predictors. Population values are determined from various published and unpublished data (Table
1). 

**Table 1 T1:** Sample effect size calculations for selected variables

		**Monotherapy treatment remission (*****n*** **= 400)**		**Combination treatment remission (*****n*** **= 240)**	
**Variable of interest**	**Observed value in the population [mean (SD) or % positive]**	**Detectable difference***	**Effect size (difference relative to variation)**	**Detectable difference***	**Effect size (difference relative to variation)**
Endpoint HDRS score	16.0 (4.9)	−1.9	0.39	−2.5	0.51
Serotonin transporter gene carriers (minor allele carriers/Caucasian)	59.9%	17%	0.31	22%	0.40
Elevated C-reactive protein (>0.22 mg/dl)	21%	13%	0.36	16%	0.48
fMRI brain score	44.1 (4.3)	1.7	0.40	2.2	0.51
Baseline Dex/CRH response (cortisol AUC, (ng*min)/mL)	2730.6 (266)	104.6	0.39	136.1	0.51
Interleukin-6 (pg/mL)	6.3 (1.4)	0.6	0.43	0.7	0.50

Thus a sample size of 400 will be adequate to detect moderate to large effect sizes in treatment remission predictors

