[136]. Although the sample sizes for differential remission by treatments will be less, with a projected overall remission rate of 30% in any group, there will be approximately 40 remitters in each group to detect the statistically significant interactions. These are reasonable numbers for the detection of large interaction effect sizes
[136].

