## Endnotes

^a^We originally intended to recruit 600 patients for PReDICT, but subject recruitment efforts with the current inclusion/exclusion criteria resulted in the reduction to 400 as the expected total number of subjects that will be successfully recruited and randomized to participation in this project.

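### Table 1's combination-phase n = 240 counts every projected non-remitter, with no allowance for dropout, refusal or missing late ratings; the two percentage rows have little or no margin for loss

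*Protocol article*

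**What the plan says.** The protocol article, under Study participants, states that the "total targeted enrollment is 400". Its endnote describes that figure "as the expected total number of subjects that will be successfully recruited and randomized", so 400 counts patients randomized, not patients completing.

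The section on statistical power and sample size states: "For these calculations, we assume a 40% remission rate". Detectable differences are defined as "the difference (either mean or proportion) between the population and the treatment remitters detectable with the given sample size", with "a Type I error rate (α) = 0.01, and a statistical power of 0.80". Table 1 then has one pair of columns for monotherapy remission at n = 400 and another for "Combination treatment remission" at n = 240. The paragraph after the table works "with a projected overall remission rate of 30% in any group".

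Under the acute monotherapy phase visits, patients who have not remitted "are offered the option to enter an additional 12-week course of combination treatment". Under Major endpoints, combination-phase remission requires a low HDRS-17 score at both week 22 and week 24.

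**The concern.** Table 1 prints a sample size for the combination phase and six detectable effects derived from it. The design can supply 240 evaluable patients only if three things all happen: no non-remitter is lost before week 12, all accept an optional further 12 weeks, and all have both late ratings. The Background itself says that many patients who fail a first treatment do not come back for another, although it gives no rate.

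At stake is how combination-phase results are read. Someone who takes the column at face value would credit a null finding with more sensitivity than a smaller evaluable sample gives. The column also sits beside a second remission rate in the same section, with no explanation of why the two differ.

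**Working it through.** **1. Where 240 comes from.** 400 × (1 − 0.40) = 240 exactly. No factor for loss or uptake is applied.

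**2. Set-up.** Alpha is 0.01; the article does not state sidedness, and two-sided is taken (z = 2.576). Power 0.80 gives z = 0.842 and power 0.90 gives z = 1.282. Remitters and non-remitters are split 40:60, following the stated 40% rate.

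**3. Continuous rows (HDRS, fMRI, cortisol, IL-6).** Detectable effect in SD units:

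d = (z_alpha + z_power) × √(1/(0.4n) + 1/(0.6n))

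- n = 240, power 0.80: 3.417 × 0.1318 = 0.45
- n = 240, power 0.90: 3.857 × 0.1318 = 0.51
- n = 400, power 0.80: 3.417 × 0.1021 = 0.35
- n = 400, power 0.90: 3.857 × 0.1021 = 0.39

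The printed combination effects are 0.50 to 0.51 and most printed monotherapy effects are 0.39 to 0.40. For example, cortisol is 136.1/266 = 0.51 at n = 240 and 104.6/266 = 0.39 at n = 400. These rows reproduce at 90% power, not at the declared 80%.

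The n that gives 80% power for 0.51 SD is 3.417² × 4.167 / 0.51² = 187. That is a loss of (240 − 187)/240 = 22%. A t-based calculation gives about 190, or 21%. IL-6, printed as 0.50, needs about 195 (19%), but its difference of 0.7 is heavily rounded.

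**4. Percentage rows (serotonin transporter 59.9%, CRP 21%).** Two-proportion test with pooled variance under the null and no continuity correction, the proportion being lower in remitters:

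power = Φ[(Δ − z_alpha × SE_pooled) / SE_unpooled]

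Serotonin at n = 240 (144 vs 96; 0.599 vs 0.379):
- SE_pooled = √(0.511 × 0.489 × (1/144 + 1/96)) = 0.0659
- SE_unpooled = √(0.599 × 0.401/144 + 0.379 × 0.621/96) = 0.0642
- power = Φ[(0.22 − 0.1697)/0.0642] = Φ(0.784) = 0.78

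Solving for the difference at 80% power gives 17.4 and 22.4 points (serotonin) and 12.5 and 15.5 points (CRP) at n = 400 and 240. The printed values are 17, 22, 13 and 16. So these rows reproduce, to rounding, at the declared 80% power with the full samples.

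**5. Effect of loss.** The loss rates are assumptions.

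| Share of 240 evaluable | n | Power, 22 points | Power, 16 points | Power, 0.51 SD | SD detectable at 80% |
|---|---|---|---|---|---|
| 100% | 240 | 0.78 | 0.84 | 0.90 | 0.45 |
| 90% | 216 | 0.73 | 0.78 | 0.86 | 0.47 |
| 80% | 192 | 0.66 | 0.72 | 0.81 | 0.50 |
| 70% | 168 | 0.59 | 0.64 | 0.75 | 0.54 |
| 60% | 144 | 0.51 | 0.54 | 0.66 | 0.58 |

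A harsher illustration combines 20% loss before week 12 with 80% uptake. If 40% remission is counted among completers, 320 × 0.60 × 0.80 = 154. If it is counted on all randomized (160 remitters), (320 − 160) × 0.80 = 128. The detectable effect is then 0.56 SD at n = 154 and 0.62 SD at n = 128, and the serotonin row becomes about 28 to 30 points.

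**6. The other remission rate.** At 30%, 400 × 0.70 = 280 non-remitters, and 240/280 = 86%. The paragraph after Table 1 is consistent with its own rate: 400/3 × 0.30 = 40 remitters per arm.

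**The case against.** The strongest reply is that the table is illustrative. The section calls the work fact-finding without prior hypotheses, and its statement that the size is adequate concerns 400, not 240. The article also admits, when explaining the open-label choice, that the combination phase lacks power to compare randomized treatments. This stands as a limit on importance: no design decision or primary analysis rests on the column. It does not justify printing an n that assumes no loss.

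Three stronger readings are tempting, and the documents do not support them.

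- A reader might infer that none of the printed combination effects can be delivered. That is wrong for the four continuous rows, which keep 80% power until roughly a fifth of the 240 are lost. Nor is this slack a concealed attrition allowance: the continuous rows match 90% power, and the percentage rows 80%, both at the full 240.
- A reader might call the percentage differences undetectable. Power of 0.66 and 0.72 at 20% loss is reduced power. The result also depends on direction. If carriers are more frequent among remitters, 22 points has power 0.87 at n = 240 and 0.82 at 216. If raised CRP is more frequent among remitters, 16 points has only 0.56 at n = 240.
- A reader might take the 30% rate as proof that 240 is too high. It points the other way: with 280 non-remitters, 240 would leave room for about 14% loss. Both rates lie within the 30% to 40% cited in the Background, and the 30% serves a different purpose. What remains is an unexplained difference.

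It is also fair that the size of the shortfall is assumed throughout.

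**Conclusion.** The point holds in a limited form. The figure 240 is every projected non-remitter among 400 randomized, although entry to the next phase is optional and its endpoint needs two late ratings. On the stated assumptions, both percentage rows are below 0.80 power at 10% loss, and the 22-point row is marginally below it already at n = 240. The continuous rows fall below 0.80 only beyond about 22% loss, because they were evidently computed at about 90% power. That is itself inconsistent with the single declared level of 0.80. The actual shortfall is unknown, since the article gives no dropout or uptake rate. The matter is a correction to a stated figure and does not affect the primary analysis.

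**What to change.** Restate the combination column at an expected evaluable n, and give the assumed rates for completing week 12, accepting combination treatment and having both week 22 and week 24 ratings. Randomization began in 2007 and recruitment was continuing at submission, so the trial's own rates may be on hand, though the article does not say so. Apply the declared 80% power to every row of Table 1, and state sidedness and, for the percentage rows, the direction of the difference. Use one remission rate throughout the section, or explain why Table 1 uses 40% and the following paragraph 30%.

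The cost is recalculating one column, plus the continuous rows of the other to bring them to the same power. The percentage-row figures become less favourable. The continuous rows change little if loss is near 20%. No extra patients are needed.

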### Aims

The primary aim of PReDICT is to identify predictors of remission with acute treatment for MDD; predictors comprise genetic, endocrine, immune, and personality measures, as well as baseline and early-treatment fMRI of the central nervous system. Predictors will be identified by utilizing sophisticated multivariate procedures to determine which variables have clinically important and statistically significant effects for the prediction of remission and response.

A secondary aim of the project is to identify predictors of recurrence of major depression during a 21-month follow-up after acute treatment. Predictors of remission will include baseline, treatment, and post-treatment measures, detailed below.

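### Table 1 does not follow consistently from its one stated set of inputs: two effect sizes are impossible, the continuous rows fit 90% rather than 80% power, and the monotherapy HDRS row is the outcome itself

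*Protocol article*

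**What the plan says.** The section on statistical power and sample size (Protocol article) fixes the inputs once for the whole table: "For these calculations, we assume a 40% remission rate", with "a Type I error rate (α) = 0.01, and a statistical power of 0.80". The column heads give n = 400 for monotherapy remission and n = 240 for combination remission. Sidedness is not stated.

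The section first says that it illustrates effects for remitters against non-remitters. It then defines the detectable difference as the "difference (either mean or proportion) between the population and the treatment remitters detectable with the given sample size". The effect-size columns are headed "Effect size (difference relative to variation".

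The rows at issue (monotherapy / combination):

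| Row | Population value | Difference | Effect size |
|---|---|---|---|
| "Endpoint HDRS score" | 16.0 (SD 4.9) | −1.9 / −2.5 | 0.39 / 0.51 |
| "Serotonin transporter gene carriers (minor allele carriers/Caucasian" | 59.9% | 17% / 22% | 0.31 / 0.40 |
| C-reactive protein | 21% | 13% / 16% | 0.36 / 0.48 |
| fMRI score | 44.1 (SD 4.3) | 1.7 / 2.2 | 0.40 / 0.51 |
| Dex/CRH | 2730.6 (SD 266) | 104.6 / 136.1 | 0.39 / 0.51 |
| Interleukin-6 | 6.3 (SD 1.4) | 0.6 / 0.7 | 0.43 / 0.50 |

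Under Major endpoints, monotherapy remission is an HDRS-17 total below 8 at both week 10 and week 12.

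**The concern.** Right after the table, the section concludes that 400 patients are enough for moderate-to-large predictor effects. A reader should be able to regenerate each row from the inputs given, and compare rows with one another. Two effect sizes look too small for their own differences, the continuous rows look too large for 80% power, and one row offers the outcome as an example of its own predictor.

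At stake is whether the stated detectable effects can be relied on, for instance in judging which candidate predictors the trial could have found. The strict alpha was chosen on purpose ("We chose an α = 0.01 because the nature of the model building will require the testing of multiple predictors"), so a power figure that silently differs between rows blurs that choice.

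**Working it through.** **Inputs.** Alpha 0.01, taken as two-sided (my assumption); power 0.80; 40% remission, hence 160 against 240 patients (n = 400) and 96 against 144 (n = 240). z(0.995) = 2.576, z(0.80) = 0.842, z(0.90) = 1.282.

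**1. Serotonin transporter effect sizes.** The SD of a binary variable is √(p(1−p)), which is at most 0.50. The smallest possible effect sizes are therefore 0.17/0.50 = 0.34 and 0.22/0.50 = 0.44. If the true differences were 16.5 and 21.5 points before rounding, the minima are 0.33 and 0.43. The printed values are 0.31 and 0.40. At the row's own 59.9%, SD = √(0.599 × 0.401) = 0.490, which gives 0.17/0.490 = 0.35 and 0.22/0.490 = 0.45. Cohen's h gives 0.34 to 0.37 and 0.44 to 0.49, depending on direction. This step needs no assumption about test, sidedness or dropout.

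**2. Continuous rows.** d = (z for alpha + z for power) × √(1/n1 + 1/n2).
- The root is 0.1021 for 160/240 and 0.1318 for 96/144.
- At 80% power the multiplier is 3.417, so d = 0.349 and 0.450 (0.350 and 0.453 by noncentral t). Dex/CRH would be 92.8 and 119.8, against 104.6 and 136.1 printed.
- At 90% power the multiplier is 3.857, so d = 0.394 and 0.508. Dex/CRH becomes 104.7 and 135.2 (105.2 and 136.1 by noncentral t), HDRS 1.93 and 2.49, fMRI 1.69 and 2.19, interleukin-6 0.55 and 0.71. These are the printed figures to within rounding or choice of test.
- One-sided alpha moves the wrong way: at 80% power, (2.326 + 0.842) × 0.1021 = 0.323.
- Holding power at 0.80 and solving for n from Dex/CRH: n = 3.417² × (1/0.4 + 1/0.6)/d², which gives 315 for d = 104.6/266 and 186 for d = 136.1/266.
- Interleukin-6 prints 0.43 and 0.50 because the differences were rounded before division (0.6/1.4 and 0.7/1.4).

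**3. Binary differences.** The pooled-variance two-proportion formula, with the population value as reference, is solved for the difference at 80% power and the printed n.
- Serotonin transporter: 17.4 and 22.4 points as a decrease, 16.3 and 20.6 as an increase (printed 17 and 22).
- C-reactive protein: 12.5 and 15.5 points as a decrease, or 13.0 and 16.2 with continuity correction (printed 13 and 16).
- At 90% power the serotonin differences would be 19.5 and 25.1 as a decrease, or 18.2 and 22.9 as an increase.

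So the binary differences fit 80% power and the continuous rows fit 90%, both at n = 400 and 240.

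**4. Comparison.** Testing remitters against a fixed population value gives 3.417/√160 = 0.270 and 3.417/√96 = 0.349. That reproduces no continuous row at 80% power, nor at 90% (3.857/√160 = 0.305). The two-group split of remitters and non-remitters is what reproduces the printed figures. The population also contains the remitters.

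**5. Endpoint HDRS, monotherapy column.** The row does not name the scale version; I take it as HDRS-17, the scale that defines remission. A remitter scores 7 or less at week 12, which is 9 points below a mean of 16.0. Cantelli's inequality bounds the share this low, for any distribution, at 4.9²/(4.9² + 9²) = 24.01/105.01 = 22.9%. A normal distribution gives 4% to 5%. To have 40% at 7 or less with mean 16.0, the SD must be at least 9 × √(0.4/0.6) = 7.35. Even 30%, the rate used for the interaction argument, needs 9 × √(0.3/0.7) = 5.89.

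**The case against.** The section presents the table as an illustration for exploratory work, and the endnote says that 400 was set by recruitment. Much of the table can be regenerated. The C-reactive protein row reproduces in full from the stated inputs: Cohen's h for the unrounded 12.5 and 15.5 points is 0.361 and 0.479, as printed. The continuous rows are conservative at the stated power. The HDRS mean and SD come from outside data, and in the combination column an end-of-monotherapy score could be a legitimate predictor.

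All of this stands and limits the point. It does not rescue the serotonin transporter effect sizes, which fail under either formula. Nor does it reconcile 90% power in some rows with the single 0.80 stated. The outside origin of 16.0 (4.9) explains the figure but does not make it fit a sample assumed to remit at 40%.

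A reader might infer that the rows use different sample sizes, or that about 20% attrition was built in unannounced. The documents do not support that. Fixing power at 0.80 does lead to about 315 and 186 patients, but no dropout allowance is stated, and 90% power at the printed n fits more directly. Nor is the table the only support for the sample size, since a short interaction argument follows it.

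**Conclusion.** The point holds in limited form: the rows rest on different unstated inputs, most plausibly different power.
- **Certain under the table's own definition:** the serotonin transporter effect sizes 0.31 and 0.40 are impossible; about 0.35 and 0.45 is right.
- **Given two-sided alpha 0.01 and a 40/60 split:** the continuous rows overstate the detectable effect by about 0.04 and 0.06 (0.39 against 0.35, 0.51 against 0.45).
- **Given that the HDRS row is on the 17-item scale:** in the monotherapy column it is circular, and it allows at most 22.9% of patients at 7 or less against 40% assumed. Circularity is not shown for the combination column.
- **Wording:** the comparison is described in two ways, and the figures correspond to remitters against non-remitters.

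It would be tempting to conclude that 400 patients are too few. The recomputation does not support that: at the stated power the continuous rows improve, and the corrected serotonin values equal the corrected continuous ones. The adequacy statement for moderate-to-large effects survives. The correction is worth making, but it changes no design decision.

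**What to change.** Recompute all rows with one stated n, power, sidedness, comparison (remitters against non-remitters) and effect-size formula, and reword the definition of the detectable difference to match. Two consistent options:
- **Keep 80% power.** Print the continuous rows as about 0.35 and 0.45 (Dex/CRH about 93 and 120) and the serotonin effect sizes as about 0.35 and 0.45. C-reactive protein keeps 0.36 and 0.48 if Cohen's h is named as the formula for proportions. With difference over population SD it becomes 0.13/0.407 = 0.32 and 0.16/0.407 = 0.39.
- **State 90% power.** Keep the continuous rows and recompute the binary ones. The serotonin differences become about 18 to 20 and 23 to 25 points, depending on direction.

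In the monotherapy column, remove the endpoint HDRS entry or replace it with a baseline measure. If it stays in the combination column, label it as the end-of-monotherapy score.

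Separately, and minor: in the Aims, the paragraph on recurrence says "Predictors of remission will include baseline, treatment, and post-treatment measures". There, remission should read recurrence, since post-treatment measures cannot predict acute remission and the imaging section assigns the week-12 scan to recurrence.

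The cost is about an hour of recalculation and rewording, with no change to design or conduct.

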#### Predictors

##### Functional magnetic resonance imaging

Recent developments in image acquisition and data analysis now suggest that resting state studies can be reliably acquired using blood oxygen level-dependent (BOLD) fMRI
[77-79]. Temporally correlated fluctuations in regional activity can be defined using both model-driven (correlations with specific seed regions) and data-driven approaches (that is, independent components analysis or self-organizing maps). These fluctuations agree with the concept of functional connectivity, a descriptive measure of spatio-temporal correlations between spatially distinct regions. Using such methods, decreased low-frequency correlations have been reported in depression
[80-82]. These first results suggest fMRI can identify network abnormalities comparable to those previously identified using PET
[36,83]. Critical to the goal of personalized treatment, resting BOLD fMRI methods can be implemented in scans of individual patients. Resting-state BOLD fMRI scans are acquired prior to initiating treatment and at a fixed, early time-point specific for each treatment. A third fMRI is performed at the completion of the 12 weeks of acute phase treatment, to serve as a predictor of recurrence during maintenance treatment. Pre-treatment scan patterns derived using multivariate analyses and associated with the treatment outcomes will be used to determine whether pretreatment brain patterns can distinguish among outcome groups
[82,84]. A second fMRI scan, acquired early in the treatment course, will be used to assess the likelihood of response to the specific treatment assigned. These analyses will serve as a first step towards defining brain-based subtypes predictive of differential treatment outcome in major depression. The data from these studies will also be entered into more complex algorithms integrating imaging findings with behavioral, environmental, biochemical, and genetic information for individual patients.

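### As worded, the fMRI section tests outcome-linked scan patterns against the same outcomes; the 0.01 error rate and Table 1's fMRI row hold only for a score fixed beforehand or computed out of sample

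*Protocol article*

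**What the plan says.** Under Predictors, Functional magnetic resonance imaging, the article says: "Pre-treatment scan patterns derived using multivariate analyses and associated with the treatment outcomes will be used to determine whether pretreatment brain patterns can distinguish among" the outcome groups. It adds that the data "will also be entered into more complex algorithms integrating imaging findings with behavioral, environmental, biochemical, and genetic information" for individual patients. The same section names seed-region correlations, independent components analysis and self-organizing maps as ways of describing connectivity, and calls the imaging analyses a first step.

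Under Data analyses, predictors are selected for statistical significance and clinical importance, with discrimination and reclassification measures. The resulting model is left for later research to test.

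Under Statistical power/sample size, Table 1 gives the "fMRI brain score" a population value of 44.1 (SD 4.3). Its detectable differences are 1.7 (0.40 SD) for 400 patients and 2.2 (0.51 SD) for 240. The stated settings are "a Type I error rate (α) = 0.01, and a statistical power of 0.80" and "For these calculations, we assume a 40% remission rate". Population values are said to come from published and unpublished data. The article does not define the score.

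**The concern.** Table 1 treats the brain score like CRP or interleukin-6: one number per patient that owes nothing to that patient's outcome. The fMRI section can be read as describing something else, a pattern that qualifies because it goes with outcome and is then asked to separate the same outcome groups. With one sample of 400 and model testing deferred, the comparison would be circular. A score whose weights were fitted to remission separates remitters from non-remitters to some degree even when the scans carry no information.

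Two things are at stake. A test at 0.01, chosen because many predictors are examined, would no longer have a 1% false-positive rate for imaging. And the score would enter predictor selection and the integrated model with an inflated apparent effect, beside predictors that were simply measured. Resampling only the final model would not remove this, because the held-out patients' outcomes would already have shaped the score. The article proposes no such resampling; the point matters only for where the cure has to be placed.

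**Working it through.** **Inputs.** From Statistical power/sample size: N = 400, 40% remission (160 remitters, 240 non-remitters), alpha 0.01 (taken as two-sided), power 0.80, score SD 4.3. The contrast is taken as remitters against non-remitters, following "we will illustrate the effect sizes for treatment remission versus non-remission"; the next definition in that section instead compares remitters with the population. The number of imaging features p is not given, so it is an assumption and is varied.

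**1. The plan's own figure.** 1.7/4.3 = 0.395 SD, tabled as 0.40. The standard error of a standardized difference is √(1/160 + 1/240) = √0.010417 = 0.1021.
- Power 0.80: (2.576 + 0.842) × 0.1021 = 0.349 SD, or 1.50 points.
- Power 0.90: (2.576 + 1.282) × 0.1021 = 0.394 SD, or 1.69 points.

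So the row matches power 0.90, not the stated 0.80. The 240-patient column behaves the same way: 0.450 SD at 0.80 and 0.508 SD at 0.90, against 0.51 tabled. This is a separate matter and errs on the cautious side.

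**2. A score fixed in advance, no true effect.** 0.40/0.1021 = 3.92, so the two-sided chance of a difference of 0.40 SD or more is about 0.00009. For such a score the usual test holds its 1% level.

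**3. A linear score fitted and tested in the same 400 patients, no true effect.** The squared t statistic of the fitted discriminant score equals Hotelling's T². With independent noise features, T² × (N − p − 1)/[p(N − 2)] follows an F distribution with p and N − p − 1 degrees of freedom. The nominal 0.01 cut-off is t = 2.588, so t² = 6.699.
- p = 5: 6.699 × 394/(5 × 398) = 1.326; P(F > 1.326) ≈ 0.25.
- p = 10: 6.699 × 389/(10 × 398) = 0.655; P ≈ 0.77.
- p = 15: 6.699 × 384/(15 × 398) = 0.431; P ≈ 0.97.

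The expected squared separation is about p × 0.010417. Its square root is 0.23 SD (p = 5), 0.32 (10), 0.40 (15) and 0.46 (20).

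Simulation of noise data agrees:

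| Noise features | Mean separation (SD) | Significant at 0.01 | Separation of 0.40 SD or more |
|---|---|---|---|
| 5 | 0.22 | 24% | 1% |
| 10 | 0.32 | 77% | 14% |
| 15 | 0.40 | 97% | 46% |
| 20 | 0.46 to 0.47 | over 99% | 81% |

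**4. The same score under 10-fold cross-validation.** When each patient is scored from weights fitted without that patient, the mean separation is about 0 at every feature count tried (1 to 100).

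**5. Treatment-specific patterns.** With about 40 remitters per arm, as the article projects, and about 133 patients per arm (40 against 93), 5 noise features average 0.41 SD in-sample and 10 average 0.61 SD. Smaller groups need fewer features for the same inflation.

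**The case against.** The strongest reply is that the score in Table 1 may have nothing to do with the pattern in the fMRI section. No sentence connects them, and a known mean and SD from outside data fit a measure defined before this trial. That stands. A reader might infer that Table 1's fMRI row is itself wrong, or that a noise score would reach its 0.40 SD. The document supports neither: the row is sound in kind for a pre-fixed score, and the noise result depends on a feature count and an in-sample assessment that the article does not state. Nor is 0.40 SD a threshold for accepting a predictor; it is a true difference said to be detectable.

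Second, the wording is ambiguous. Patterns could be derived without the outcome and only afterwards related to it, and the methods named in the section build features that way. This also stands for the features. It does not settle how they are weighted or chosen, which is where circularity would enter.

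Third, fold structure is the kind of detail an article leaves to an analysis plan, and that plan is not shown. Its absence is therefore no fault. The point rests instead on what the sentence does say: outcome-linked patterns are used to judge separation of the outcome groups.

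Fourth, the work is described as exploratory. That lowers the stakes, but the same article sets an alpha of 0.01 because multiple predictors will be tested, and that level should mean what it says.

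**Conclusion.** The concern holds in conditional form. Followed literally in the single trial sample, the fMRI wording makes the imaging test circular. If weights are fitted or selected on these patients' outcomes and assessed in the same patients, the false-positive rate at a nominal 1% is about 24% with 5 independent noise features and about 77% with 10, and the mean separation reaches 0.40 SD at about 15. These figures assume a linear score, 160 against 240 patients and independent features. Correlated imaging features have a smaller effective number, so their raw count would overstate the inflation. Table 1's detectable difference applies to a score fixed beforehand or computed out of sample, and not to one trained in-sample. The article does not say which kind its brain score is.

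**What to change.** Reword the sentence in the fMRI section so that the scan pattern is either (a) fixed before any trial outcome is used, for example from the earlier data behind the 44.1 (4.3) if those data define the score, or (b) derived inside each cross-validation fold, so that each patient's score comes from a pattern fitted without that patient. Enter only that fixed or out-of-fold score in the predictor tests and in the model under Data analyses. Define the brain score, and add a note to Table 1 that the fMRI row assumes a score of this kind.

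No new data are needed. The cost is wording, more computing for option (b), and a smaller reported imaging effect.
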